#### Economic evaluation plan

Cost comparisons will be made between the mindfulness course and the standard care. Service cost data will be combined with the primary outcome measures (HADS) and quality-of-life measures generated from the EQ-5D-3L to assess cost-effectiveness. If the intervention has lower costs and better outcomes, then it will be ‘dominant’. In the event of the intervention having higher service costs and better outcomes, cost-effectiveness will be assessed using incremental cost-effectiveness ratios. To address uncertainty in cost and outcome differences, we will run different sensitivity analyses, as tornado diagrams, worst-best scenarios or cost-effectiveness acceptability curves. The results of this economic evaluation should be treated with caution as the study is underpowered. However, the results will give an indication of the potential cost-effectiveness of the mindfulness intervention.

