### Aims

The overall objective of this study is to assess the feasibility of procedures and processes as well as potential efficacy (i.e. explore potential for detecting change in each of the proposed measures for each group) of a mindfulness-based intervention (MBI) for people with PD, which will be delivered via Skype.

The specific aims of this trial are to:Monitor rates of recruitment, retention, refusal, adherence to the mindfulness sessions, and homework practice, as well as the appropriateness of eligibility criteria to determine the rate of each for planning the main trialAssessing time and resource problems, for example whether it is feasible for patients to answer all the questionnaires and the time taken to do so, the flow of participants entering the study, the use of equipment to set up Skype, and other resources neededDetermine data management issues, by monitoring levels of missing data and data variabilityEvaluate the potential for detecting a change in each of the proposed outcome measures (anxiety, depression, pain, fatigue, insomnia, quality of life, subjective well-being, physical impact of PD, health costs) when comparing the mindfulness-based intervention (MBI) group to the wait-list control (WLC) groupUnderstand the mechanisms of change (mindfulness skills, acceptance, self-compassion, decentering, tolerance of uncertainty) in each patient group, including any potential nocebo effects in the WLC groupAssess the qualitative experiences of receiving the mindfulness intervention and people’s views and experiences of using Skype as a mode of delivery as well as people’s feedback on the questionnaires used

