### Wait-list control group

9pt?>Participants allocated to the WLC group will receive the treatment they would normally expect from the National Health Service (NHS) in the UK. People may receive a mix of clinical input and review from both primary and secondary care providers, according to individual health needs. Access to psychological assessment and intervention for people with PD is inconsistent across the UK, and dedicated psychological services are extremely scarce [29]. People in the WLC group will be offered the opportunity to take part in the MBI at the end of the 20-week follow-up.

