#### Health economics measures

Participants of both arms will be measured using the assessments described below.

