#### Feedback interview procedure

At the end of the 8-week intervention period, participants, in the MBI group, will also be included to be interviewed by an MSc health psychology student who has not had any involvement in other aspects of the trial. Participants will be asked to give open and honest accounts of their experiences and opinions of the intervention (see topic guide, Table 3). Questions address expectations regarding the intervention, experiences of MBI sessions, features of the intervention liked and disliked, and the process of change (or not) as a result of the course. Each interview will be digitally recorded. Interviews will be anonymised and transcribed; any information that may compromise confidentiality will be omitted before the transcripts come to the research team.

**Table 2 Tab2:** Details and schedule of the MindPD trial assessment procedure

Assessments administered	Screening (week 0)	Baseline (week 1)	Mid-intervention (week 4)	Post-intervention (week 8)	3-month follow-up (week 20)
Main details sheet	X				
Telephone Interview for Cognitive Status Instrument modified version (TICS-M)	X				
Demographics sheet		X			
Primary outcome measure:					
Hospital Anxiety and Depression Scale (HADS)		X	X	X	X
Secondary outcome measures:					
Parkinson’s Disease Activities of Daily Living Scale (PADLS)		X	X	X	X
Brief Pain Inventory (BPI)		X	X	X	X
Fatigue Severity Scale (FSS)		X	X	X	X
Insomnia Severity Index (ISI)		X	X	X	X
Process variables:					
Self-Compassion Scale (SCS)		X	X	X	X
Philadelphia Mindfulness Scale (PHLMS)		X	X	X	X
Experiences Questionnaire (EQ)		X	X	X	X
Acceptance Action Questionnaire (AAQ-II)		X	X	X	X
Intolerance of Uncertainty Scale (IUS-12)		X	X	X	X
Health economics variables:					
Subjective Well-Being questionnaire (SWB)		X		X	X
EuroQoL and visual analog scale (EQ-5D-3L and VAS)		X		X	X
ICEpop CAPability Measure for Adults (ICECAP-A)		X		X	X
Adult Social Care Outcomes Toolkit (ASCOT)		X		X	X
Home practice				X	X

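### A between-arm cost-effectiveness analysis is planned, but no scheduled assessment is described as recording service use or cost during follow-up

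*Protocol article*

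**What the plan says.** The fourth specific aim in the Aims section names the outcomes on which the two arms will be compared. The list includes "quality of life, subjective well-being, physical impact of PD, health costs".

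The Economic evaluation plan sets out the comparison: "Cost comparisons will be made between the mindfulness course and the standard care". It continues: "Service cost data will be combined with the primary outcome measures (HADS) and quality-of-life measures generated from the EQ-5D-3L to assess cost-effectiveness". Two results are then provided for. The first is "If the intervention has lower costs and better outcomes, then it will be ‘dominant"; the second is "In the event of the intervention having higher service costs and better outcomes, cost-effectiveness will be assessed using incremental cost-effectiveness ratios".

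On data collection, the Health economics measures section opens with "Participants of both arms will be measured using the assessments described below". It then describes subjective well-being (SWB), EQ-5D-3L with EQ-VAS, ICECAP-A and ASCOT. Table 2, the assessment schedule, has a block headed "Health economics variables" with the same four entries, each at baseline, week 8 and week 20.

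The Wait-list control group section describes the comparator as usual NHS care: "People may receive a mix of clinical input and review from both primary and secondary care providers, according to individual health needs".

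**The concern.** The analysis needs a cost for each participant in each arm, and the schedule describes no means of obtaining one. Every other outcome in the fourth aim can be traced to an instrument in Table 2; health costs cannot.

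Without service-use data there is no cost difference to set against the HADS or EQ-5D-3L difference. An incremental cost-effectiveness ratio would then have no valid numerator. The pilot would also give the main trial no information on whether people with Parkinson's disease can report their service use, how complete such data are, or how variable the costs are. The study's feasibility aims ask exactly these questions of its other measures.

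**Working it through.** The plan states no figure on this point, so there is nothing to reproduce. The check sets the analysis against the schedule.

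**1. Rows of Table 2, by content**

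| Content | Rows |
|---|---|
| Main details sheet (screening only) | 1 |
| TICS-M cognitive screen (screening only) | 1 |
| Demographics sheet (baseline only) | 1 |
| HADS | 1 |
| Daily activities, pain, fatigue, insomnia | 4 |
| Process measures (SCS, PHLMS, EQ, AAQ-II, IUS-12) | 5 |
| Health economics (SWB, EQ-5D-3L and VAS, ICECAP-A, ASCOT) | 4 |
| Home practice | 1 |
| **Total** | **18** |

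Rows described as recording service use or cost during follow-up: 0 of 18.

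**2. Could an existing row serve?**

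- The two information sheets are given once each, at screening and at baseline. Whatever they contain, they cannot record service use up to week 20.
- ASCOT, as the article describes it, covers attributes such as personal safety, control over daily life and social participation. It rates how the person is doing, not how much care was received.
- The home practice diary records frequency and duration of meditation.

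**3. Could the cost of the course alone be enough?** Write the incremental cost as

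ΔC = C(course) + [S(MBI) − S(WLC)],

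where S is the mean cost of other services used in an arm up to week 20.

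- C(course) can be built from trial records. The article gives eight 1-hour sessions in groups of five. With 30 in the MBI arm that is 30/5 = 6 groups, 6 × 8 × 1 h = 48 facilitator contact hours, or 48/30 = 1.6 hours per participant, plus preparation, supervision and equipment.
- The wait-list arm is offered the course only after week 20, so its course cost within follow-up is zero and C(course) > 0.
- If the bracket is not measured, ΔC = C(course), which is always positive, and the plan's lower-cost result could never occur. That result needs S(MBI) − S(WLC) < −C(course).

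The plan's own wording therefore presupposes wider service costs in both arms.

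**4. Could usual care be costed as a fixed package?** No. The Wait-list control group section says that it varies with individual need across primary and secondary care. A single assumed package applied to both arms would also set the bracket to zero by construction.

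**5. Is another source described?** The article mentions no extraction from medical records and no use of routine data.

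**The case against.** The strongest reply is that this is a condensed article and that Table 2 is not exhaustive. The Quantitative analysis plan adds retrospective then-test items to two questionnaires, and these have no row. The contents of the main details and demographics sheets are not shown. A service-use form may sit in the full protocol.

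That limits the claim: the document supports only that no such measure is described here. It does not remove the point. The then-test items are additions to questionnaires for outcomes already scheduled, not a new source of data. Table 2 is itemised down to the information sheets and home practice, and it has a dedicated economics block. The one input that the cost analysis depends on is absent from both the text and the table.

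A second reply is that the plan already calls the economic results underpowered and only indicative. That caveat concerns imprecision; a larger sample would not supply cost data that were not collected.

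A reader might go further and infer three things that the document does not support.

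- **The decision rule is defective because it names only two of the four cost–outcome combinations.** Higher cost with worse outcome is conventionally dominated, acceptability curves are among the listed options, and full decision rules are commonly left to an analysis plan.
- **The listed sensitivity analyses are wrong and net monetary benefit with bootstrapping is required.** That is a preference; the plan states no wrong method.
- **A probability can be given for the observed outcome difference favouring control.** It would rest on an assumed effect size, standard deviation or correlation that the document does not give, and it would not measure the missing cost data.

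**Conclusion.** The point holds as a contradiction between the analysis and the assessment schedule. Health costs are a named outcome, and service costs are a named analysis input, but 0 of the 18 scheduled rows is described as measuring either during follow-up. On this schedule the delivery cost of the course can be estimated; the between-arm difference in service costs cannot.

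This rests on two assumptions: that Table 2 and the Health economics measures section reflect what is collected, and that service costs mean more than course delivery, which the lower-cost result requires. It would be wrong to conclude that the trial certainly holds no cost data, because an unseen full protocol could contain a form. If it does, the remedy is to name it in the schedule.

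The consequence is moderate. The economic evaluation is exploratory, and the feasibility, clinical and qualitative aims are unaffected.

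**What to change.** Choose one of two routes.

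1. **Collect the data.** Add a brief self-report service-use questionnaire to the economic assessments already scheduled at baseline, week 8 and week 20, in both arms, each covering the period since the previous assessment. Name it under Health economics measures and in Table 2. If such a form already exists, only the naming is needed. The cost is an amendment and a few minutes of extra burden per assessment, in a battery whose burden is itself under study. The Recruitment and consent process section says that recruitment has begun, so baselines already completed would lack the form. Participants already past week 8 would miss that assessment too. Both should be reported as missing.

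2. **Narrow the claim.** Restrict the health-cost outcome in the Aims, and the Economic evaluation plan, to the delivery cost of the course, built from session, attendance and equipment records. Drop the between-arm cost-effectiveness analysis, and bring the Abstract and Discussion into line. This adds no participant burden, but the pilot then says nothing about cost-effectiveness or about collecting service-use data in the main trial.

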#### Qualitative analysis plan

The interviews will be analysed using inductive thematic analysis. The inductive analysis is a process of coding the data without trying to fit it into a pre-existing coding frame or the researcher’s analytic preconceptions [51]. The analysis will be conducted following Braun and Clarke’s guidelines [52]. The analysis of the transcripts will be conducted in parallel with ongoing data collection. First, each coding unit in the first transcript will be given a code name, using vocabulary as close as possible to that used by participants themselves [53] to avoid prematurely importing preconceptions into the analysis. This procedure will be repeated on the second transcript. When the same themes reoccur, they will be provided with the same label. Initial codes will then be applied systematically to the entire dataset, giving full and equal attention to each data item. As data analysis, proceeds codes will be re-defined as new and alternative themes arise. Earlier transcripts will be re-coded as codes are developed and refined. During this analysis, the validity of individual themes in relation to the dataset will be considered and also whether the themes reflect the dataset as a whole. A detailed paper trail will record the development of the codes and the relationship between the raw data and the refined themes and codes. Further, framework analysis techniques [54] will be used, where the final codes will be tabulated to inspect the data for patterns and relationships in the themes between people with PD.

## Discussion

Mindfulness-based interventions have been shown to effectively reduce anxiety, depression, and pain in patients with chronic physical illnesses, including PD [14]. Mindfulness-based interventions have been traditionally delivered in a face-to-face group setting [55]. This pilot trial will look specifically at assisting psychological adjustment for people with PD and is conducted in preparation of an efficacy study for an online MBI in PD. The distance delivery of this trial means that we are offering psychological support to a group of patients who would not otherwise routinely have formal access to psychological interventions but who nonetheless are faced with considerable psychological challenges. With this study, we will explore different ways to deliver group psychological interventions and we will enrich our knowledge on the specific needs and challenges faced by people affected by PD as well as how best to address these needs.

Some limitations of the current study need to be acknowledged. First, we will not have a large enough sample to account for the heterogeneity in the non-motor challenges that people with PD face. Therefore, we will not be able to make sub-group comparisons of the potential effectiveness of the interventions for people who entered the trial with different non-motor challenges. Further, a WLC group can induce nocebo effects [56], inflating the effectiveness of the intervention. Any worsening of symptoms for the WLC group will be reported and suggestions will be made for more appropriate controls in a future larger trial. Also, the total HADS [31] score may not be the most appropriate tool to detect caseness of depression and anxiety [57]. However, it was chosen since HADS measures anxiety and depression without confounding by somatic symptoms of the physical disorder, in contrast to other depression and anxiety scales that include items like insomnia, retardation of psychomotor, tremor, dry mouth, muscle aches, loss of energy, and fatigue. These items although they are an indication of anxiety or depression, they can also be symptoms of PD and not a reflection of anxiety or depression. There are also some validation studies for HADS showing good psychometric properties [58–61]. In addition, HADS will potentially be chosen as the primary outcome of the intervention and it was important to choose a measure that is sensitive to change both during the course of an illness and in response to medical or psychological intervention [33, 62]. HADS is also relatively short and easy to administer. Finally, Skype calls depend on the strength of the internet connection and can interrupt therapy sessions. AB has experience delivering these courses over Skype without excessive technical problems [23, 63]. AB usually incorporates any disruptions or lack of quality as examples that participants could use to practise staying with difficulties and identify thoughts arising when there is frustration, so these interruptions become part of the mindfulness learnings. The qualitative interviews with participants at the end of the courses will help us explore experiences of the course and the Skype delivery. These interviews will direct us to potential changes in the future courses.

Nevertheless, this pilot trial will answer important questions about the feasibility of procedures and processes as well as the potential efficacy of an 8-week distance-delivered mindfulness course in reducing distress and increasing the quality of life. If the results show that this intervention is feasible and potential effective for people with PD, a grant will be prepared for a large randomised control trial which will aim to assess the effectiveness of this intervention on a representative sample and compared against an active control group. We will also explore the role of different ‘active ingredients’ of mindfulness-based approaches such as acceptance, self-compassion, decentering, and cultivating mindfulness skills to determine how mindfulness interventions work and which are the most important components of these interventions regarding changes in outcome measure. Further, this pilot trial will provide some indication regarding the cost-effectiveness of the intervention and its acceptability to patients.

This pilot trial is set up to be methodologically robust and to conform to CONSORT guidelines. We have taken care to address key sources of bias; the MBI for PD course will be subject to ongoing supervision to ensure therapy fidelity, and this will also be checked post-therapy by independent raters. The assessments of patient outcomes are self-reported and collected by an independent researcher who is uninvolved in therapy delivery. The MBI trial for PD also benefits from service-user input from the early stages of therapy design and manual development, right through to the in-depth evaluation of the MBI sessions. The data from the feedback interviews will be particularly important in guiding any changes to the MBI format.

## Abbreviations

CBT: Cognitive behavioural therapy
GCP: Good Clinical Practice
MBI: Mindfulness-based intervention
MBCT: Mindfulness-based cognitive therapy
NHS: National Health Service
NRES: National Research Ethics Service
PD: Parkinson’s disease
WLC: Wait-list control
